## Abstract

**Background:**

Seroma after breast cancer surgery is a frequent entity; therefore, different products have been described in literature with the aim to reduce it. The most studied ones have been the sealants products, being tested with aspirative drains. Symptomatic seroma represents the 19% after axillary lymphadenectomy without drains. The aim of this study is to analyze the effect of a sealant in the seroma control after axillary lymphadenectomy without drains and identify the risk factors related to symptomatic seroma.

**Methods:**

This is a prospective, multicenter, international, and randomized clinical trial. Patients undergoing conservative surgery and axillary lymphadenectomy for breast cancer will be randomized to control group (lymphadenectomy without sealant) or interventional group (lymphadenectomy with sealant Glubran 2®). In any of the study groups, drains are placed. Patients who received neoadjuvant treatment are included. Measurements of the study outcomes will take place at baseline; at 7, 14, and 30 days post-surgery; and at 6–12 months. The primary outcome is symptomatic seroma. Secondary outcomes are seroma volume, morbidity, quality of life, and lymphedema.

**Discussion:**

Several studies compare the use of sealant products in axillary lymphadenectomy but generally with drains. We would like to demonstrate that patients who underwent axillary lymphadenectomy could benefit from an axillary sealant without drains and reduce axillary discomfort while maintaining a good quality of life. Assessing the relationship between axillary volume, symptoms, and related risk factors can be of great help in the control of seroma in patients who received breast cancer surgery.

**Trial registration:**

ClinicalTrials.gov, NCT05280353. Registration date 02 August 2022.

## Introduction

### Background and rationale {6a}

Breast cancer (BC) represents a major health problem due to its high incidence, being the most frequent cancer in women and the most diagnosed cancer worldwide.

According to data from the Spanish Society of Medical Oncology [1], a total of 34,750 new cases of BC were diagnosed in Spain in 2022 with a 5-year prevalence of 144,233 in 2020 [1]. The estimated number of new BC cases for 2022 is 34,750 [1].

Axillary involvement has classically been considered the most important prognostic factor in BC. For decades, axillary lymphadenectomy (AL) has been performed for the purpose of staging, control, and improved survival in patients with BC. The clinical practice of surgical management of the axilla underwent a major change following the study published by Giuliano et al. [2], with a decrease in the number of ALs performed worldwide. Today, AL is still the treatment of choice in patients with node involvement (pN +), both those undergoing primary surgery and after neoadjuvant treatment, being this last scenario controversial to date.

However, the morbidity of AL is not negligible. Different series report the following prevalence of complications associated with the surgical technique: chronic lymphedema in the upper extremity (20–30%), seroma (50–60%), wound infection (5–15%), frozen shoulder syndrome (up to 10%), neuropathic pain due to intercostobrachial nerve injury (5–20%), and other less frequent complications such as hematoma, scapular winging (long thoracic nerve injury), or latissimus dorsi muscle atrophy (latissimus dorsi bundle injury).

The most common complication after AL is seroma (15–90% depending on series) [3]. Seroma is defined as the presence of serous fluid in the areas of surgical resection or dissection. Seroma is mainly seen after mastectomy and AL. Although the basis of seroma formation is not fully understood, factors such as surgical technique, extent of dissection, and sealing devices used may influence its control [4].

The usual clinical practice in these procedures includes the placement of an axillary aspirative drain, which is usually removed when the amount of drainage collected is low enough. However, this clinical practice is questioned by some authors [5]. Given its high incidence, several groups have made efforts to achieve a reduction and better control of seroma [3], noting that most of them use suction drains after surgery. According to the conclusions published by Cochrane in 2013, there is limited evidence that the insertion of a drain after axillary lymphadenectomy reduces the likelihood of developing seroma and/or reduces the number of aspirations needed to control it [5]. Given the current evidence regarding the use of drains after lymphadenectomy, in our study, we decided not to use drains after regular axillary lymphadenectomy.

Efforts to control and reduce the seroma volume after AL and therefore help our patients improve their recovery and have a better QoL have been made but without any significant results that lead us to change clinical practice yet. Some teams suggest the use of sealants and/or biological glues [6]; however, to date, there are still no relevant results to allow clinical practice to change [7]. Studies assessing the use of such sealants include patients with and without drains. Currently in breast cancer, percentages close to 20–25% of symptomatic seroma requiring drains are described [8, 9].

There is a large amount of conflicting scientific evidence regarding current management of seroma after AL. However, there is a lack of evidence stablishing a relationship between the volume of the axillary seroma and its symptoms. Moreover, the effect of tissue sealants in seroma control without using suction drains has not been sufficiently investigated either. For this reason, the present study is a randomized multicenter international clinical trial that aims to analyze the role of a tissue sealant in seroma production and in the control of pain-related-to-seroma in patients with BC undergoing LA without a drain placement.

Glubran 2® is a synthetic surgical glue with a cyanoacrylic base modified by the addition of a monomer synthesized by the manufacturer, approved for its use in surgery for its hemostatic, sealing, and adhesive properties that facilitate strong tissue adhesion. Its active ingredient is N-butyl-2-cyanoacrylate + methacrylosulpholane.

Some authors consider and demonstrate that after reducing the axillary space in AL, either by means of sealants or by a surgical approximation of tissues, a reduction in seroma is achieved. However, there is even evidence of a reduction in the percentage of seroma in patients in whom Glubran 2® is applied after breast cancer surgery [10].

We have designed the current study with the product Glubran 2® to demonstrate that, through its sealing and adhesive properties at axillary level, could reduce the axillary seroma rate.

## Objectives {7}

### Main objectives

To evaluate the efficacy of Glubran 2® in reducing the percentage of symptomatic seroma after AL without drainTo assess the safety and tolerability of Glubran 2® in breast cancer surgery after AL without drain

### Secondary objectives

To assess whether there are differences in axillary seroma volume and its relationship to symptomatic seroma between groupsTo assess whether there are differences in the number of punctures required, as well as the volume aspirated between groupsTo assess the existence of risk factors related to symptomatic seromaTo compare morbidity between study groups in the short and long termTo assess whether there are differences in seroma volume, symptomatic seroma, and final nodal anatomy between groupsTo assess quality of life (QoL) after the intervention as measured by the EQ-5D-5L questionnaire (Spanish version)

### Main hypothesis

The use of Glubran 2® after AL in patients with BC can safely reduce the symptomatic seroma percentage.

### Justification

The administration of an axillary sealant after AL (without the use of drain) could reduce the number of symptomatic seroma and therefore require fewer axillary punctures/evacuations, thus improving the quality of life of patients.

### Trial design {8}

This is a multicenter, international, prospective, double-arm randomized clinical trial with a superiority design. Baseline data will be measured prior to randomization. Follow-up data will be collected at 7, 14, and 30 days after randomization. Long follow-up data will be collected at 6 and 12 months. A CONSORT diagram is presented in Fig. 1.

**Fig. 1 Fig1:**
[figure not shown]
CONSORT Flow diagram

### Eligibility criteria {10}

Inclusion criteria
Over 18 years oldConservative surgery for BC with associated AL

Exclusion criteria
Need for mastectomyHistory of ipsilateral axillary radiotherapyASA 4 patients (selected ASA 3 patients)Lack of adequate cognitive capacity and/or failure to sign the informed consent form

In all the cases, surgeons (general surgeon or a gynecologist) will perform the intervention during breast cancer surgery.

### Who will take informed consent? {26a}

During the standard preoperative clinical assessment, all BC patients who are candidates for surgery meeting the inclusion criteria will be informed of the possibility to participate in the present study by the surgeon. The patient will give their authorization by signing an informed consent document during the base-line visit.

### Additional consent provisions for collection and use of participant data and biological specimens {26b}

Patients enrolling this study gave informed consent to be followed-up during the study period and to allow the use of their medical records according to the trial’s objectives, for academic purpose. This trial does not include biological specimens.

## Interventions

### Explanation for the choice of comparators {6b}

Symptomatic seroma is the comparator chosen to prove if a sealant has an effect after AL in patients without drain. All patients are treated following the current breast cancer guidelines; therefore, the criteria for performing AL are uniform among participating hospitals. Pain is a usual symptom after axillary surgery; however, we wanted to evaluate if there is the use of a sealant agent has any role in pain control in this patients. We chose the QoL EQ-5D-5L questionnaire because it also allows to check the upper extremity mobility.

### Intervention description {11a}

The AL will be performed in all cases with a sealing device such as LigaSure®, Harmonic Focus®, or similar. The incision may be chosen by the surgeon at each of the participating centers. AL will be performed according to standard technique, including Berg levels I and II and level III if necessary.

After AL is performed, Glubran 2® will be placed in the axillary hollow in the study group. The product will be applied homogeneously in all participating centers. For this purpose, training lessons have been held in each hospital, with both visual material and the presence of a product expert on the field. After washing the armpit with physiological saline, assuring it is completely dry and caring for an exhaustive control of hemostasis, the product should be applied using its specific applicator (yellow). It has to be distributed over the entire lymphadenectomy area including the following: the area above the axillary vein, the area below the axillary vein, around the latissimus dorsi bundle, the lateral costal wall including the vascular-nerve bundle, the serratus muscle, and the subcutaneous cellular tissue. The closure of the subcutaneous cellular tissue and the skin will be led to the standard in each participating center, although the most common technique is the closure of the subcutaneous cellular tissue with simple stitches of resorbable multifilament suture and the closure of the skin with a continuous intradermal suture of resorbable monofilament thread.

### Hospitalization regime and analgesic regimen

Patients will be operated on an outpatient or conventional inpatient basis, according to the criteria of each hospital participating in the study.

The recommended analgesia at discharge will consist of paracetamol 1g/8 h alternating with metamizole 575 mg/8 h for the first 7 postoperative days in all patients. The need to extend this regimen will be assessed at the different clinical follow-up visits. In case of allergy or intolerance, the regimen will be adapted with two alternating analgesics.

The performance of a neurological block prior to surgery will be recorded.

### Criteria for discontinuing or modifying allocated interventions {11b}

In accordance with the Declaration of Helsinki, participants can withdraw from the trial at any time and for any reason.

The withdrawal criteria is as follows: patients will be excluded from the study in any of the following scenarios: (a) the patient expresses their willingness to leave the study, (b) the patient is not able to accomplish the established clinical controls, (c) continuation of the study procedures may be detrimental to the patient’s health or well-being, (d) there is a concurrent illness that prevents compliance with patient monitoring and assessment procedures.

### Strategies to improve adherence to interventions {11c}

A breast cancer nurse in each center will be the responsible to check that the clinical visits and ultrasound sessions are met and in the adequate timing. They will also be the contact person for patients in case of doubts about their condition or any questions related to the study.

### Relevant concomitant care permitted or prohibited during the trial {11d}

All aspects of clinical care will be permitted as long as they are registered in the medical records.

### Provisions for post-trial care {30}

If any side effect occurs due to the use of Glubran 2® or any other action concerting the study, it will be covered by the hospital’s insurance.

## Outcomes {12}

### Primary outcome

Percentage of patients with symptomatic seroma, defined as a seroma requiring its puncture-aspiration.

Seroma puncture-aspiration is indicated in the following scenarios during follow-up:Tension seroma causing uncontrollable pain (VAS = 5) even though taking the recommended oral analgesia (paracetamol 1 g/8 h alternating with metamizole 575 mg/8 h)Seroma volume not allowing a full adduction of the upper limb and causing discomfort as a result

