### Secondary endpoints

Number of seroma aspiration-punctures requiredPain (measured by visual analogue scale, VAS)Axillary seroma volume (measured by axillary ultrasound in cm.^3^)Number of post-operative emergency room visitsNeed for hospital readmissionPresence of lymphoedema in the armQoL after the intervention (measured by the EQ-5D-5L questionnaire, Spanish version)

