### Sample size {14}

Accepting an alpha risk of 0.05 and a beta risk of 0.2 in a bilateral contrast, 67 subjects in each study arm are required to detect a statistically significant difference in the percentage of patients with symptomatic seroma (which is expected to be 25% for the control group and 7% for the study group). A loss to follow-up rate of 10% has been estimated.

For the calculation of “*n*” and due to the large extent of seroma described in the literature, reference values of 25% described in the study by Jan et al. [9] have been taken.

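### One of the two puncture routes that define symptomatic seroma is a judgement about seroma volume, so the planned analysis of ultrasound volume against symptomatic seroma is biased towards an association

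*Protocol article*

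**What the plan says.** Under Outcomes {12}, Primary outcome, the endpoint is "Percentage of patients with symptomatic seroma, defined as a seroma requiring its puncture-aspiration". Two indications for puncture follow:

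- Pain route: "Tension seroma causing uncontrollable pain (VAS = 5) even though taking the recommended oral analgesia".
- Adduction route: "Seroma volume not allowing a full adduction of the upper limb and causing discomfort as a result".

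The Secondary objectives include assessing axillary seroma volume and its relation to symptomatic seroma. The Discussion paragraph of the abstract also presents the link between axillary volume, symptoms and risk factors as something the trial will help to clarify. Background and rationale {6a} gives the reason: "there is a lack of evidence stablishing a relationship between the volume of the axillary seroma and its symptoms".

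The Secondary endpoints list volume ("measured by axillary ultrasound") and pain ("measured by visual analogue scale, VAS") as separate items. The text under Participant timeline {13} says that visits collect VAS, analgesic adherence, presence of symptomatic seroma, need for puncture and quality of life. Nothing in the article says that the two puncture indications will be told apart in the volume analysis.

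**The concern.** A variable should not be tested as an explanation of an outcome that is partly assigned by reference to that variable. A patient who is punctured by the adduction route has, in the clinician's judgement, a seroma large enough to block movement. Ultrasound volume will tend to be high in such patients whether or not volume has anything to do with pain. When both routes are pooled into one yes/no outcome, the analysis cannot separate large seromas that produce symptoms from large seromas that met the puncture rule partly because of their size. This is incorporation bias.

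What is at stake is the interpretation of one secondary, observational objective, which addresses a gap that the protocol itself names. Volume would carry the same problem into the logistic risk-factor model of Statistical methods {20a} if it were entered there. The article does not say that it will be.

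**Working it through.** **Inputs from the article (Sample size {14}).** Design: "Accepting an alpha risk of 0.05 and a beta risk of 0.2 in a bilateral contrast". Symptomatic seroma: "which is expected to be 25% for the control group and 7% for the study group". There are 67 patients per arm (134 in all), with 10% loss. The mean event rate is (25% + 7%)/2 = 16%.

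**The plan's own figure.** With the arcsine formula, h = 2(arcsin√0.25 − arcsin√0.07) = 2(0.5236 − 0.2678) = 0.5117. Then n = 2(1.960 + 0.842)²/h² = 2 × 7.849/0.2618 = 59.96 evaluable per arm, and 59.96/0.9 = 66.6, so 67 per arm. The stated size reproduces, and the present point does not depend on it.

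**Inputs not in the article (assumptions).** These are the share s of punctures made by the adduction route, how closely clinical judgement follows ultrasound volume, and how strongly that route selects the largest seromas. Pain is set independent of volume throughout, so any association beyond 5% rejections comes from the adduction route alone.

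**Two simulations, Mann-Whitney test at two-sided 0.05, 1,500 runs each.**

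- *Milder rule:* 134 patients. The adduction-route rate is p₂ = 0.16s, drawn at random from the 40% with the largest judged volume. The pain-route rate is p₁ = 1 − 0.84/(1 − p₂). At s = 50%, p₂ = 0.08, p₁ = 0.087, and the chance of an adduction-route puncture within the top 40% is 0.08/0.40 = 0.20.
- *Stricter rule:* 120 patients (about 134 × 0.9). The adduction route takes exactly the top fraction 0.16s of judged volume. The pain route takes the top 0.16(1 − s) of an independent pain score.

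Judgement is either perfect, or noisy with a correlation to true volume of about 1/√2 = 0.71.

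| Share by adduction route | Milder, noisy | Milder, perfect | Stricter, noisy | Stricter, perfect |
|---|---|---|---|---|
| 0% | 5% | 4% | about 5% | about 5% |
| 10% | 6% | 8% | not run | not run |
| 25% | 11% | 21% | 29% | 43% |
| 50% | 36% | 67% | 78% | 92% |
| 75% | 71% | 97% | 97% | 99.7% |
| 100% | 97% | 100% | not run | not run |

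The table gives the chance of p<0.05. At a 50% share the AUC of volume for the pooled outcome is 0.61 to 0.66 under the milder rule and 0.70 to 0.76 under the stricter one.

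**Hand check of one cell (milder, perfect, 50%).** Half of the events (0.08 of 0.16) have a mean volume rank of 0.80, the middle of the top 40%. Everyone else has mean rank (0.5 − 0.08 × 0.80)/0.92 = 0.474. The mean rank of all events is (0.80 + 0.474)/2 = 0.637. Solving 0.637 = 0.16 × 0.5 + 0.84 × AUC gives AUC = 0.66, which agrees with the simulation.

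The spread between the two rules shows how far the answer depends on how strongly the adduction route selects large seromas.

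**The case against.** The strongest reply is that the adduction route is not a volume criterion in the strict sense. It has no cm³ cut-off and uses no ultrasound reading, and it requires both restricted movement and discomfort. Those are symptoms, and the stated gap concerns symptoms in general, not pain alone. A seroma that limits the arm is symptomatic, so part of any association with volume would be real. This stands. It is why the adduction route should not be dropped from the volume analysis, and why the bias is one of degree.

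A second reply is that VAS pain is its own endpoint and is collected at visits together with analgesic adherence, so pain-route punctures can largely be recognised. This stands in part. It makes the fix easy, but the stated objective relates volume to symptomatic seroma, not to VAS. Visits outside the schedule are left to the surgeon's discretion, so a VAS score may not accompany every puncture. The full eCRF is not shown and may already hold an indication field. The point rests on the stated definition and the stated objective, not on the absence of that field.

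A third reply is that the simulations take pain as unrelated to volume and assume the route share. This is correct, and the figures are illustrations over a range, not predictions.

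A reader might infer that the volume analysis must come out positive whatever the truth. The documents do not support that. At a 25% share the test rejects in 11–43% of runs, and detection is close to certain only when the adduction route dominates.

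**Conclusion.** The point holds as a limited one. The pooled outcome partly contains the variable that a secondary objective relates it to, so that analysis is biased towards an association. With pain independent of volume, the chance of p<0.05 is about 11–43% at a 25% adduction-route share and 36–92% at 50%. With no punctures by that route it stays at the nominal 5%. These ranges rest on an assumed share, an assumed link between clinical judgement and ultrasound volume, and an assumed selection rule, none of which the article gives. Some of any observed association would be genuine, and the pooled outcome cannot say how much.

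A reader might also infer that the primary result is compromised, or that the trial has no other measure of symptoms. Neither follows. The randomised comparison of puncture rates applies one definition to both arms and does not use ultrasound volume as an explanatory variable. The sample size reproduces and is unaffected. VAS pain is recorded separately. This is a cheap improvement to the interpretation of a secondary objective.

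**What to change.** Leave the primary outcome and the puncture indications as they are, and make three changes:

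1. Record in the eCRF, at the time of each puncture, which of the two indications led to it, allowing for both.
2. State that the volume objective will relate ultrasound volume, measured before any aspiration, to VAS pain and to each puncture route separately, alongside the pooled outcome. A reading taken after aspiration would reflect the treatment.
3. Report the associations with the pooled outcome and with the adduction route as partly definitional. Treat any risk-factor model that includes volume in the same way.

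The cost is one eCRF field and a sentence or two in the analysis plan. The drawback is fewer events per route: at 16% of 134 there would be about 21 punctured patients, so an even split leaves about 11 per route. Analysing VAS as a continuous measure in all patients partly offsets this and needs no new data.
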